## Abstract

**Introduction:**

Falls have major implications for quality of life, independence and cost to the health service. Strength and balance training has been found to be effective in reducing the rate/risk of falls, as long as there is adequate fidelity to the evidence-based programme. Health services are often unable to deliver the evidence-based dose of exercise and older adults do not always sufficiently adhere to their programme to gain full outcomes. Smartphone technology based on behaviour-change theory has been used to support healthy lifestyles, but not falls prevention exercise. This feasibility trial will explore whether smartphone technology can support patients to better adhere to an evidence-based rehabilitation programme and test study procedures/outcome measures.

**Methods and analysis:**

A two-arm, pragmatic feasibility randomised controlled trial will be conducted with health services in Manchester, UK. Seventy-two patients aged 50+years eligible for a falls rehabilitation exercise programme from two community services will receive: (1) standard service with a smartphone for outcome measurement only or (2) standard service plus a smartphone including the motivational smartphone app. The primary outcome is feasibility of the intervention, study design and procedures. The secondary outcome is to compare standard outcome measures for falls, function and adherence to instrumented versions collected using smartphone. Outcome measures collected include balance, function, falls, strength, fear of falling, health-related quality of life, resource use and adherence. Outcomes are measured at baseline, 3 and 6-month post-randomisation. Interviews/focus groups with health professionals and participants further explore feasibility of the technology and trial procedures. Primarily analyses will be descriptive.

**Ethics and dissemination:**

The study protocol is approved by North West Greater Manchester East Research Ethics Committee (Rec ref:18/NW/0457, 9/07/2018). User groups and patient representatives were consulted to inform trial design, and are involved in study recruitment. Results will be reported at conferences and in peer-reviewed publications. A dissemination event will be held in Manchester to present the results of the trial. The protocol adheres to the recommended Standard Protocol Items: Recommendations for Interventional Trials (SPIRIT) checklist.

**Trial registration number:**

ISRCTN12830220; Pre-results.

## Introduction

Falls are an important public health issue, with over 30% of people aged 65 and over falling at least once a year.^1^ This has implications for quality of life, independence and cost to the health service.^1^ Strength and balance training (SBT) comprises ‘carrying out exercises that increase muscle strength in the legs and improve balance’.^2^ Strength and balance exercise programmes are effective in reducing risk and rate of falls and injuries.^3^ Sherrington *et al*
4 have shown that for strength and balance programmes to be effective they need to be progressive, tailored and of adequate dose (3× a week for 50 hours, and then maintained). Work carried out by Public Health England^5^ illustrates that to see a return on investment, fidelity to the evidence-base has to be carried out (adequate dose, progression).

However, Nyman and Victor^6^ report that adherence to evidence-based strength and balance programmes is poor. The National Health Service (NHS) only delivers programmes that are predominantly 3 months or less,^7^ older adults do not carry out their exercise programme three times a week as prescribed (dose) or carry out the programme for a sufficient length of time to achieve and maintain the benefits.^6 7^ Cost and appropriate staffing are cited as primary reasons for short NHS delivery.^7^

Unless there are innovative new solutions to support the delivery of falls prevention exercises sufficiently to reduce falls risk and to prevent re-referral to services, over the coming decade it is estimated that population changes will result in service demand beyond the reach of current interventions.^8^The use of smartphones to support falls rehabilitation could be one of the solutions. The proportion of older adults using smartphones is growing rapidly, with 39% of those aged 65 to 74% and 15% of those aged over 75 using smartphones.^9^ Smartphones offer multiple opportunities to support healthy ageing and falls prevention as they are portable, can be body-worn and can therefore be used for falls detection, movement detection and motivation^10–12^ The evidence which looks at the role of the smartphone for falls prevention is sparse,^13^ particularly for interventions focused on rehabilitation/SBT. Although there is a lack of specific evidence related to falls prevention interventions, there is evidence that older adults find mobile phones more usable than using a new device, for example a falls alarm.^14^ It has also been suggested that barriers to smartphone use in this population can be overcome through adequate support and affordability.^15^ There is evidence supporting the use of mobile phone-based healthy lifestyle programmes,^16 17^ including to increase physical activity.^17–19^ King *et al*
11 developed and tested smartphone applications (apps) based on behaviour change theory designed to motivate adults aged 45+years. One of these included personalised goal-setting and behavioural feedback, successful evidence-based behavioural change techniques.^20^ The apps recieved positive feedback from participants and increased physical activity.

We know from previous studies that attitudes and beliefs are important to the uptake of and adherence to exercise by older adults.^21 22^ The theory of planned behaviour (TPB)^23^ is particularly useful for assessing older adults’ attitudes in relation to exercise uptake and adherence.^21 22 24^ The TPB is based on three core components:

Perceived behavioural control (PBC), the perceived ease or difficulty of performing the behaviour.Social influences, including subjective norms (beliefs of important people, eg family), perceived social support (support from others for behaviour) and modelling (following observed behaviour of others).Attitudes (outcome expectations).^23^ Focused on the advantages and disadvantages of the behaviour (outcome expectations) and when related to adherence, whether these advantages have occurred.

Attitudes measured by using a TPB-based tool have been significantly associated with exercise behaviour in an earlier study.^21^ This theory has informed the intervention overall and content of the motivational messages within the proposed intervention (focused on outcome expectations/PBC).

Smartphone technology-based motivational applications underpinned by behaviour change theory and developed with health professionals and older adults could be an effective way of encouraging maintenance of exercise and of successfully supporting adherence to evidence-based SBT. We have already carried out usability and acceptability testing of the technology and two motivational apps (one for health professionals and one for patients), before planning this trial. The smartphone apps have been developed through several cycles of user-led design. Initially we carried out engagement workshops with older adults (AgeUK) and health professionals from one falls service in Manchester, followed by usability/acceptability testing with another falls service in Manchester and their patients (Integrated Research Application System. IRAS:205980). The use of this approach has enabled us to develop the apps, establish whether the technology is acceptable to older adults and health professionals (qualitative methods) and to check its usability (technology testing). Overall, the apps were acceptable to both patients and health professionals with the majority of suggested changes made to the health professionals’ app to ensure it fit more easily with their practice. Changes following this testing included improvements in the delivery of messages and a more streamline approach to scheduling activities for the health professional. Another suggested change was to make smartphone pens available to participants to aid in the use of the touchscreen.

This study now aims to explore whether it is feasible for smartphone technology to be used to support patients to sufficiently adhere to an evidence-based exercise rehabilitation programme. As a secondary aim it will assess whether technology-based outcome measures (smartphone-based falls alarm and timed up and go test (TUG))^25^ are reliable when compared with standard methods (eg, falls calendars). Through a feasibility randomised controlled trial (RCT) we will explore the feasibility of using smartphone technology to support falls rehabilitation and test study procedures (eg, suitability of outcome measures, SD of the outcome measure, recruitment, randomisation, follow-up rates, retention, time required for analysis). Both arms of the trial will receive rehabilitation exercises and will report their exercises on a study provided smartphone but only the intervention arm will carry out goal setting and receive feedback through the phone.

The intervention has the potential to:

Increase the amount of support the patient receives to adhere to their exercise, leading to increased adherence.Increase exercise progression/dose which could be cost neutral/saving.Enable health professionals to monitor compliance to the prescribed programme.

This could assist maintenance of health, reducing long-term falls risk and re-access to services.

## Methods

### Trial design

Core trial information is presented in table 1. This study is a two-arm pragmatic feasibility RCT including the collection of economic data. The trial design framework is exploratory. Alongside the trial, qualitative work is carried out to understand the feasibility of the intervention and the trial procedures.

**Table 1 T1:** WHO trial registration data set

Data category	Information
Primary registry and trial identifying number	ISRCTN:12 830 220
Date of registration in primary registry	21.08.2018
Secondary identifying numbers	
Source of monetary or material support	National Institute for Health Research Postdoctoral Fellowship Award
Primary sponsor	University of Manchester
Secondary sponsor	N/A
Contact for public queries	[contact]
Contact for scientific queries	[contact]
Public title	The TOGETHER trial
Scientific title	Can smartphone technology be used to support an effective home exercise intervention to prevent falls among community dwelling older people? The TOGETHER feasibility RCT
Countries of recruitment	UK
Health condition of problem studied	Falls in older adults
Interventions	**Standard service:** **Manchester City**: 12 weeks once a week contact (home or group exercise), check-ups until 6 months discharge. **Trafford:** 8-week group exercise once a week or 6-week home exercise then discharged or referred to further 8-week group exercise. **Control:** For all prescribed exercise plan and exercise booklet given, asked informally what they want to achieve (outcome goals). Use of study provided smartphone for reporting exercises and falls detection as outcome measures only **Intervention:** standard service (as above) plus the use of ‘Motivate me’ (health professional app) and ‘My activity programme’ (patient app) on study provided smartphones.
Key inclusion and exclusion criteria	**Age:** older adults aged 50+ **Sex:** male or female **Inclusion:** at risk of falls, referred to falls rehabilitation services and assessed as suitable for an exercise programme, good 3G/4G reception in their home or wifi. **Exclusion:** unable to follow instructions (unless they have support from a family member or carer), Severe visual impairment, long-term residential or nursing care, terminal illness or expected shortened lifespan, defined as less than 6 months, older adults unable to read written English unless they have support from a family member or carer).
Study type	Interventional Allocation: randomised; Primary purpose: prevention, feasibility
Date of first enrolment:	20th September 2018
Target sample size	72
Recruitment status	Pending
Primary outcome	Feasibility of the design and procedures
Key secondary outcomes	Balance (Berg), function (TUG/mTUG), falls (calendar/FallsMonitor@home), strength (30 s chair stand), fear of falling (Short FES-I), health-related quality of life (EQ-5D-5L/ ICE-CAP-O), resource use, adherence (my activity programme/EARS). Baseline, 3, 6 months.

EARS, Exercise Adherence Rating Scale; EQ-5D-5L, European Quality of Life 5 Dimensions; FES-I, Falls Efficacy Scale-International; ICE-CAP-O, ICEpop CAPability measure for Older people; ISRCTN, International Standard Randomised Controlled Trials Number; mTUG, Mobile based instrumented timed up and go test; TUG, timed up and go test.

### Sampling principles and procedures

#### Eligibility

Older adults at risk of falls (aged 50+years) and assessed as requiring a falls rehabilitation exercise programme are identified through current community falls rehabilitation services delivered in Manchester City and Trafford. The two sites see patients from diverse socioeconomic populations. Exclusions include older adults who are unable to follow instructions (unless supported by a family member/carer), who are unable to understand written English (unless supported by a family member/carer), with severe visual impairment, those in long-term residential or nursing care and those with terminal illness or expected shortened lifespan, defined as less than 6 months, as determined by the NHS teams. Patients need to have good 3G/4G mobile phone reception (able to access webpages) or wifi in their home and this is assessed by the health professional before they handout participant information or by the researcher when taking consent.

#### Recruitment, consent, sample size

Health professionals give patients the study information sheet and inform them about the intervention. The health professionals then ask the patient if they are happy to be contacted by the researcher who demonstrates the technology either in the patient’s home or within groups at each NHS site. The technology is demonstrated to the participant before they are asked to give informed consent. Where possible a former patient who has used the smartphone applications accompanies the researcher to demonstrate the technology. We think involvement of a peer has the potential to assist in promoting patient confidence in the use of the technology.

The first 36 eligible patients identified through each service (n=72 in total) who are willing to participate are being recruited and randomised (figure 1). Thirty patients per arm after attrition (approx. 10%) are normally used for feasibility RCTs.^26^ Study participants are randomised using a computer-generated randomisation algorithm at sealedenvelope.com, stratified by gender and site, using block randomisation (2, 4, 6 blocks) into either intervention or control group. Stratification is by gender and site to ensure equal distribution across sites as we are testing all trial procedures.

**Figure 1 F1:**
[figure not shown]
Consort diagram.

#### Blinding

Baseline and follow-up (3 and 6 months) assessments are carried out by experienced clinicians within each NHS Trust (not a member of the clinical teams participating), who are blinded to which intervention the participants are receiving; at baseline the individual is also blinded to the intervention they will receive as randomisation occurs after baseline assessment.

As this is an ‘active’ intervention, it is not possible to blind the health professionals delivering the service or the participants during the intervention. The lead researcher provides technical support to both arms to use the smartphone so is not blinded.

The statistical analysis will be carried out by the lead researcher with the support of a statistician. Patient ID codes will be removed from the data to allow for blinded analysis.

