#### Control application for self-reporting exercise

The control arm receives a study phone with a basic app where they report their exercises, but they are only able to report their exercises (outcome measure), they are not able to view their programme, receive messages or receive feedback on the phone. The health professional is not able to view what they have reported (outcome measure for the research team only), thereby minimising risk of contamination.

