### Analysis

Quantitative data are analysed using SPSS Release V.22.0. The main analyses is descriptive, involving the estimation of recruitment rates, attrition rates, non-compliance rates, means and SD of outcomes by group at baseline and end trial, and 95% CI for differences of means of outcomes between groups and assessment of change following the intervention at end trial. The health economics analysis is focused on informing relevant measures and means of collection of health-related quality of life and resource use for the future definitive study. Only an exploratory cost-effectiveness analysis will be conducted; for all measures we will report mean values and sample variability alongside information on missing values.

Data from the smartphone-based outcome measures (FallsMonitor@home, mTUG, My activity programme/control self-report app) will be compared with the traditional measures (falls calendar,^32^ TUG,^25^ EARS^39^) alongside qualitative feedback as part of their validation. A statistical analysis plan will be created before data analysis.

Qualitative interviews/focus groups will be analysed using thematic analysis.^44^ The research will be inductive and although will seek to further understand the quantitative findings, this approach will also generate categories and explanations directly from the data rather than based on previously set aims and objectives, reducing risk of bias.^44^ QSR International's NVivo V.10 qualitative data analysis software will be used to manage the data. The validity of the analysis will be checked by returning to the data once themes have been identified and also through the use of a second researcher who will check samples of analysis. The accuracy of the transcripts will be checked through discussion with participants to establish if anything is not clear from the interviews/focus groups.

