### Trial monitoring

The lead researcher ([name]) will monitor the delivery of the intervention and recruitment of patients; there will also be a clinical lead ([name]) at each site taking overall responsibility for identification of patients and delivery of the intervention. This team, alongside academic experts ([name]) from the Trial Co-ordination Group will ensure overall quality of trial data. The AG meets bi-annually, giving feedback on the project, providing expert guidance and assisting in dissemination; this includes two previous patients. A risk register is reviewed by the AG. The study is subject to the audit and monitoring regime of the University of Manchester and the monitoring plan followed.

A detailed risk assessment has been carried out and potential patient, organisational and study hazards considered, the likelihood of their occurrence and the resulting impact should they occur.

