## Discussion

This is the first trial that we are aware of that explores the potential use of motivational smartphone apps for the support of an evidence-based falls exercise programme.

As this is an active intervention and control we are unable to blind participants or those delivering the intervention. However, the design does enable us to blind those carrying out both the assessments and analysis. The fact that both arms have a smartphone minimises the risk of unblinding with the independent assessors and, we would argue, also reduces risk of drop-out. There is the potential for the control group to become motivated by reporting their activities. However, if we did not ask them to report, there is also the risk of any difference between groups being a function of differential reporting schedules rather than a function of the intervention per se.

We provide participants with study phones, which may be different to using the app on their own phones. However, we need to ensure the smartphone meets the technical specification required for FallsMonitor@home to work correctly. Furthermore use of study phones enables us to maintain confidentiality of participants (if phones are lost we can wipe them remotely).

This trial assesses several novel outcome measures against the gold standard, the mTUG against standard TUG, the FallsMonitor@home against standard calendar method and a self-report app against the EARS tool.^39^ This enables us to further our understanding of whether technology has the potential to provide more objective and reliable outcome measures than current methods.

We use two very different NHS sites, reflecting the reality of day-to-day practice (one specialist falls service, one general rehabilitation services) to explore the delivery of the intervention. This means that the standard service is different across the two sites adding complexity to how the control and intervention arm are delivered. However, these differences enable us to assess its scalability to full trial where different types of falls services would need to be included as sites. It also enables us to be more representative of current services and assess its potential for delivery in practice.

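### The analysis is described as blinded, but the named analyst is the unblinded lead researcher, and removing patient ID codes does not mask the arm

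*Protocol article*

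**What the plan says.** Four statements in the protocol article bear on this.

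- Blinding, on the lead researcher's status: "The lead researcher provides technical support to both arms to use the smartphone so is not blinded".
- Blinding, on who analyses: "The statistical analysis will be carried out by the lead researcher with the support of a statistician".
- Blinding, on how masking is achieved: "Patient ID codes will be removed from the data to allow for blinded analysis".
- Discussion, after conceding that participants and those delivering the intervention cannot be blinded: "the design does enable us to blind those carrying out both the assessments and analysis".

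Trial monitoring adds that the lead researcher "will monitor the delivery of the intervention and recruitment of patients". The Analysis section plans a "95% CI for differences of means of outcomes between groups" and an "assessment of change following the intervention at end trial". It also says that an SAP will be written before the data are analysed.

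**The concern.** The person declared unblinded is the person named to analyse, yet the analysis is twice presented as blinded. The masking step acts on the patient identifier, whereas blinding an analysis means concealing the allocation.

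The Discussion offers blinded analysis as a counterweight to the unavoidable lack of blinding elsewhere, so readers are asked to rely on it. At stake is the credibility of results that leave room for analyst judgement. One example is scoring app-reported exercise against a prescribed plan that can change, to decide whether the 80% adherence threshold is met. Others are the between-arm differences and the effect sizes that the Outcome measures section intends for the definitive trial's sample-size calculation.

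**Working it through.** The plan gives no figure to reproduce here. The check sets the passages side by side, with one piece of illustrative arithmetic.

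**Step 1: who knows the allocation, and who analyses?** Blinding says the lead researcher is not blinded, because of technical support given to both arms. Trial monitoring gives the same person oversight of delivery and recruitment. Blinding then assigns that person the statistical analysis, with a statistician in support. The named analyst is therefore someone who knows allocations from trial contact.

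**Step 2: what does the masking step remove?** Taking out the patient ID code removes the direct link from a record to a named person. It does nothing to the allocation variable. A between-group difference in means, with its confidence interval, cannot be computed without a variable separating the groups. The article states no coding of that variable and no holder of a key. The step can mask only indirectly, by making it harder for the analyst to match a record to a remembered participant and so to a remembered arm.

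**Step 3: how strong is that indirect protection?** Inputs: 72 patients in total and stratification by gender and site (Recruitment, consent, sample size); two sites; age, falls history and health conditions also recorded (Outcome measures).

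- Site-by-gender cells: 2 × 2 = 4.
- Average patients per cell: 72 / 4 = 18.
- Average per cell and arm: 72 / (4 × 2) = 9.

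The number per site is fixed at 36, but the gender split is not stated. The figures of 18 and 9 are averages and describe each cell only if the cells are equal in size, which is an assumption. With an unequal split some cells would be smaller. Adding age and falls or medical history to site and gender makes it plausible that someone who supported these participants could recognise many of the records. If the arms carried coded labels, a few such recognitions would be enough to reveal which code is which.

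**Step 4: compare with the claim.** The Discussion says the design blinds those carrying out the analysis. Steps 1 to 3 show an unblinded analyst, a step that does not act on allocation, and weak indirect protection. The unqualified claim does not follow from the design described.

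**The case against.** The best defence is that the two statements concern different stages. The lead researcher is unblinded during the trial because of technical support; stripping IDs then closes the route from a record to a known participant. If the arms were also coded, this would be a coherent, if weak, form of masked analysis. Arm coding and key holding are commonly left to an SAP or full protocol, and an SAP is promised, so their absence from an article is no fault in itself. This stands, and the point does not rest on that absence. It rests on what the article does state: an unblinded analyst, a masking step directed at the wrong variable, and an unqualified claim built on them.

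It is also fair that the trial is exploratory, its main analysis is descriptive, and the physical outcomes are measured by blinded assessors. This limits the consequence.

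Four stronger readings are tempting but unsupported:

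- *Removing IDs destroys linkage.* A reader might infer that baseline could no longer be paired with follow-up, or smartphone measures with standard ones. The article does not say when IDs are removed. They could be stripped after visits and sources are merged, or replaced by a new key. This needs clarifying but is not an established error.
- *The group label stays visible in the file.* An arm variable is needed, but the article does not say whether it is labelled or coded.
- *App data reveal the arm.* Control participants use a basic app in which "they are not able to view their programme, receive messages or receive feedback on the phone". But the app outcome planned for comparison is self-reported exercise, which both arms enter; the Analysis section does not list messages or feedback among the variables.
- *The lead researcher has a personal stake in the app.* The Introduction says the team developed the apps. It states no personal interest of the lead researcher.

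**Conclusion.** The concern holds as an internal contradiction. The Blinding section names an unblinded person as analyst, while that section and the Discussion describe the analysis as blinded. The stated step does not by itself mask allocation, and in a trial of 72 patients at two sites it gives only weak protection against recognition.

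The importance is moderate. What is affected is the credibility of the between-arm estimates, and of the effect sizes carried into planning the definitive trial. The recruitment and retention counts and the blinding of the assessors are not called into question. No size of bias can be derived from the documents, and none is claimed. The conclusion assumes that the lead researcher described as unblinded is also the one who runs the analysis, which is what the text says. It also assumes that no masking step beyond ID removal supports the claim in the article.

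**What to change.** Choose one of two routes.

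1. **Withdraw the claim.** Delete the blinded-analysis statement from Blinding, amend the Discussion sentence, and claim blinding for the outcome assessors only. This changes wording and nothing else.
2. **Make the claim true.** Replace the ID sentence with a procedure along these lines: the arms are coded A and B; the key is held by someone outside the analysis; a pseudonymous study ID is kept so that visits and data sources stay linked; the supporting statistician, provided they have no participant contact, runs the between-arm comparisons under the SAP finalised before analysis; and the key is released once those results are fixed. The Discussion should then limit its claim to the assessments and the coded comparisons.

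The second route costs a modest shift of analysis time to the statistician. The article does not state that statistician's independence or capacity, so both need to be confirmed. Neither route changes the trial design or adds to the burden on patients.
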